## Abstract

**Background:**

The prevention of obesity and improvement of academic achievement in children are concerns of industrialized societies. Obesity has been associated with psychological disorders, including attention deficit hyperactivity disorder, whose prevalence has been estimated at 6.8 % in Spanish children and adolescents. It is known that physical activity is positively related to academic achievement and negatively related to the risk of obesity in children. However, studies to test the effectiveness of physical activity interventions in improving academic achievement in preschool children are scarce and have some weaknesses that threaten their validity. Moreover, very few studies have examined their effectiveness in improving symptoms of attention deficit hyperactivity disorder. This paper outlines a two-year multidimensional preschool intervention (Movi-Kids) aimed at preventing obesity and improving academic achievement in children with or without attention deficit hyperactivity disorder.

**Methods/Design:**

Twenty-one schools from Ciudad Real and Cuenca, Spain, were randomized to intervention and control groups. In the first academic year, children in the third grade of preschool and the first grade of primary school in the intervention group received the Movi-Kids intervention. In the second academic year, schools were crossed over to the other group. The intervention included children, parents and teachers, and the school environment, and consisted of: (i) three hour-long sessions of recreational non-competitive physical activity after school, weekly, (ii) educational materials for parents and teachers addressing sedentary lifestyle risks and (iii) playground modifications to promote physical activity during breaks. Primary outcome measures of this study were academic achievement (intelligence, cognition, memory, attention and perception), assessed by the Battery of General and Differential Aptitudes, and adiposity measures (body mass index, waist circumference, triceps skinfold thickness and body fat percentage). Secondary outcome measures were: attention deficit hyperactivity disorder risk, motor skills, health-related quality of life and sleep quality. These variables will all be measured in both groups at baseline and at the end of the first and second academic years.

**Discussion:**

It seems reasonable that an intervention to promote physical activity based on playground games will be useful for simultaneously improving academic achievement and controlling obesity.

**Trial registration:**

ClinicalTrials.gov NCT01971827.

## Background

The analysis of the relationship between physical activity and academic achievement is an emerging concern, owing to the alarming decrease in physical activity levels in schoolchildren at young ages and social pressure to achieve academically. Physical activity and fitness have been positively related to academic achievement in schoolchildren [1, 2]. This association has been explained by the structural changes that physical exercise generates in the brain, such as neurogenesis, angiogenesis, increased hippocampal volume and connectivity [3, 4].

Many cross-sectional studies support a positive relationship between physical activity, fitness, cognitive development and academic achievement in children and adolescents [1, 5]. However, a recent systematic review [6] of randomized controlled trials warns of the scarcity of studies that assess the effectiveness of interventions promoting physical activity in order to improve academic achievement or cognitive skills in children and adolescents. Moreover, this review [6] concludes that more rigorous trials using adequate sample sizes, standardized interventions, valid and reliable tools of measurement, and long-term follow-up for sustained cognitive and psychosocial outcomes are needed.

The figures relating to childhood obesity in Spain and other Western countries represent a major public health concern [7, 8]. The current prevalence of overweight and obesity in children aged 6 to 8 years from Castilla-La Mancha is 36.8 % [9], similar to other areas in Spain [10]. Obese children are at increased risk of becoming obese adults [11, 12], and the risk of adult obesity is much greater, as earlier adiposity rebound occurs [13, 14], a crucial period in the development of obesity. Excess weight in childhood is associated with different cardiovascular risk factors [15] and other health problems, such as obstructive sleep apnoea [16], psychological disorders [17], low academic achievement [16] and poor quality of life [18]. However, the interaction between genes, environment and lifestyle factors has been considered critical in the development of childhood obesity [19, 20]; among lifestyle factors, physical activity plays a central role in the prevention and treatment of this problem [21, 22].

The latest Cochrane review [23] highlights that there is consistent evidence regarding the effectiveness of interventions for preventing obesity in children aged 6 to 12 years. However, studies that address the effectiveness of such interventions in children younger than 6 years are scarce [23]. Only one study analyzed a healthy lifestyle promotional intervention (Ballabeina) in predominantly migrant preschool children, with successful effectiveness in reducing adiposity and improving fitness [24].

According to the Diagnostic and Statistical Manual of Mental Disorders, fifth edition (DSM-5) [25], attention deficit hyperactivity disorder (ADHD) is characterized by a persistent and impairing pattern of inattention, hyperactivity or impulsivity. A consistent body of evidence confirms that ADHD is often associated with other psychiatric conditions, such as specific learning disorders, mood and anxiety disorders, and sleep disturbances [26]. The aetiology of ADHD is complex and multidimensional, and combines both genetic and environmental factors. However, early diagnosis and appropriate treatment can positively influence its evolution [26–28]. In terms of prevalence, ADHD is one of the most common neurodevelopmental disorders in early childhood, affecting from 4.9 to 8.8 % of children and adolescents in Spain [29].

Interest has grown in the comorbidity between ADHD and other psychiatric and medical conditions. Clinical and epidemiological studies have consistently associated ADHD with overweight and obesity [30, 31]. Three mechanisms have been proposed to explain this relationship: (1) it has been suggested that two obesity-related factors, binge eating and excessive daytime sleepiness, might occur in children with ADHD, (2) obesity and ADHD share genetic and neurobiological abnormalities, such as dysfunctions in brain reward pathways, and (3) impulsivity and inattention are associated with irregular and dysregulated eating patterns, which contribute to weight gain [31].

Conversely, several researchers have described the relationship among physical exercise and stress, anxiety, depression, behavioural problems, impulse control, improvement of interpersonal relationships, academic achievement and working memory in ADHD children [32–34]. These benefits of physical activity in children with ADHD might be mediated by changes in levels of stress hormones and serotonin, although evidence in this regard is inconclusive, since, as a recent meta-analysis [35] underlines, very few studies have examined the effect of physical activity interventions on symptoms such as inattention, hyperactivity or impulsivity, anxiety and cognitive functions in children with ADHD, and those studies have all been conducted in children older than 7 years.

Thus, this paper reports on the rationale and methods of a trial aimed at assessing the effectiveness of a multidimensional physical activity intervention (Movi-Kids) for improving academic achievement and adiposity in school children, with or without ADHD, aged 4 to 7 years from Castilla-La Mancha, Spain. The secondary objectives will be to estimate the prevalence of ADHD in this age group of schoolchildren, and to assess the effectiveness of this programme for improving children’s levels of physical activity (during break time), motor skills, health-related quality of life and sleep quality.

This project is coordinated with another project that shares the same population-based sample, which is aimed at assessing the effectiveness of a physical activity intervention for preventing obesity and reducing cardiovascular risk during the adiposity rebound period in children from Castilla-La Mancha, Spain (ClinicalTrials.gov: NCT01971840) [36].

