#### Exclusion criteria

Children who had any of the following conditions were excluded: (a) severe Spanish language learning difficulties, (b) serious physical or mental disorders identified by parents or teachers that would impede participation in the programme’s activities, or (c) those with diagnoses of chronic disorders, such as heart disease, diabetes or asthma, which in the opinion of their paediatricians would prevent their participation in the programme’s activities.

Schools with only one full third-grade class of preschool or one first-grade class of primary school were excluded.

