#### Secondary outcome measures

##### Attention deficit hyperactivity disorder risk

We used the Attention Deficit Hyperactivity Disorder Rating Scale-IV, which has been translated into a Spanish version and validated [40]. It is a screening and evaluation scale of ADHD that includes two subscales, for inattention and hyperactivity, and a total score. Each item represents each of the ADHD symptoms, according to the criteria of the Diagnostic and Statistical Manual of Mental Disorders [41]. We used the parents’ and teachers’ version, which fits the criterion of ‘the presence of symptoms in at least two environments’.

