### Statistical analysis

The sample size was estimated to be able to show differences between the control group and the intervention group of 2 % (alpha error, 0.05; statistical power, 0.80) in mean body fat at the end of the first year. The estimated sample size was 140 children per group; this figure was multiplied by an inflation factor for cluster-randomized trials [51], which was estimated at 1.1264 using measurements from previous studies in body mass index [52]. To examine subgroup differences (e.g., sex, age, ADHD or socio-economic status) under the same conditions, and estimating a 15 % dropout rate, the minimal sample size was estimated at 1600 children (800 per group).

The statistical analysis will be carried out in two phases. In the first, we will verify that the randomization was effective in creating two comparable groups, examining the differences between the control and intervention groups in mean body fat and academic achievement. After that, we will identify outliers and extreme values, and their trustworthiness. Finally, we will check the adjustment of the variables to the normal distribution by using the Kolmogorov–Smirnov test and graphical procedures (normal probability plot).

In the second phase, we will assess the change between the intermediate and final evaluation variables in the first and second years of the study. Mixed regression models [53] will be estimated using each outcome variable as a dependent variable at the end of the first and second years of the study. The different models will be adjusted for baseline values, age and school (cluster), and the interventions will be treated as fixed affects (1 = intervention group, 0 = control group).

The results will be expressed as absolute differences in change in variables between the baseline and the final measurements (confidence interval of 95 %). When the dependent variable is the prevalence of overweight or obesity, the odds ratio will be calculated, together with a 95 % confidence interval.

Because of the different patterns of weight and height, triceps skinfold thickness and body fat, the models will be separately implemented for boys and girls. A separate analysis will also be conducted for ADHD (with or without), socio-economic status, origin (native or foreign), area (urban or rural), and state-funded or private school.

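### The ADHD prevalence objective and the ADHD subgroup rest on a rating scale alone, so the design can estimate the prevalence of a positive screen but not of the disorder

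*Protocol article*

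**What the plan says.** The Background of the protocol article sets this aim: "The secondary objectives will be to estimate the prevalence of ADHD in this age group of schoolchildren". The Statistical analysis section adds a subgroup on the same footing: "A separate analysis will also be conducted for ADHD (with or without").

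The measurement sections describe something narrower. The section on ADHD risk introduces the ADHD Rating Scale-IV with the words "It is a screening and evaluation scale of ADHD that includes two subscales, for inattention and hyperactivity, and a total score". Parent and teacher versions are both used, a choice "which fits the criterion of ‘the presence of symptoms in at least two environments". The Abstract names the endpoint as risk: "Secondary outcome measures were: attention deficit hyperactivity disorder risk, motor skills, health-related quality of life and sleep quality". Table 1, presented as covering every variable measured, lists ADHD risk by this scale and has no entry for a diagnosis.

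The Background, following DSM-5, says that ADHD "is characterized by a persistent and impairing pattern of inattention, hyperactivity or impulsivity".

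**The concern.** One measurement carries two names. As an endpoint it is ADHD risk. As an objective and as a subgroup it is ADHD. A symptom scale completed by two informants records the presence of symptoms in two settings. It does not establish the impairment that the article's own definition requires, and no clinical interview or confirmation follows a positive result.

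Two conclusions are at stake:

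- **The prevalence estimate.** A screen-positive rate equals the prevalence of the disorder only when false positives happen to balance missed cases. Its confidence interval describes sampling error and says nothing about this bias.
- **The subgroup effect.** If the intervention effect depends only on true status, the effect among screen-positive children is a weighted average of the effects in true cases and in non-cases. The weight on true cases is the positive predictive value (PPV). Reporting it as the effect in children with ADHD claims more than was measured.

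**Working it through.** The article states no precision target, cut-off, sensitivity or specificity for this objective, so there is no figure of its own to reproduce. The check asks how far a screen-positive rate could lie from the true prevalence.

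**Inputs from the article**
- Prevalence p = 6.8% in Spanish children and adolescents (Abstract), with a range of 4.9% to 8.8% (Background).
- Minimum sample of 1600 children and cluster inflation factor of 1.1264 (Statistical analysis).

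**Assumptions, not in the article**
- Sensitivity (Se) 0.60 to 0.90 and specificity (Sp) 0.85 to 0.99.
- The cited prevalence applies to ages 4 to 7.
- The inflation factor, which was derived for body mass index, also serves for a positive screen.

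**Formulas**
- Screen-positive rate = Se × p + (1 − Sp) × (1 − p)
- PPV = Se × p / screen-positive rate

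**Results at p = 0.068**

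| Se | Sp | True positives | False positives | Screen-positive rate | PPV |
|---|---|---|---|---|---|
| 0.60 | 0.99 | 0.0408 | 0.0093 | 5.0% | 81% |
| 0.80 | 0.99 | 0.0544 | 0.0093 | 6.4% | 85% |
| 0.80 | 0.95 | 0.0544 | 0.0466 | 10.1% | 54% |
| 0.80 | 0.90 | 0.0544 | 0.0932 | 14.8% | 37% |
| 0.90 | 0.85 | 0.0612 | 0.1398 | 20.1% | 30% |

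The first and last rows are the extremes of the screen-positive rate over the assumed ranges. The same corners give 3.9% to 18.7% at p = 4.9%, and 6.2% to 21.6% at p = 8.8%.

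**Where the conclusions turn, at Se = 0.80 and p = 0.068**
- The bias is zero when (1 − Sp) × 0.932 = 0.20 × 0.068 = 0.0136, so Sp = 0.985. Below that the rate is too high, above it too low.
- True and false positives are equal when (1 − Sp) × 0.932 = 0.0544, so Sp = 0.942. Below that most screen-positive children do not have ADHD, above it most do.

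**Comparison with sampling error**
- The 95% half-width at p = 0.068 is 1.96 × √(0.068 × 0.932 × 1.1264 / 1600) = 0.013, or 1.3 points.
- At Se = 0.80 the bias is 10.1 − 6.8 = 3.3 points with Sp = 0.95, and 14.8 − 6.8 = 8.0 points with Sp = 0.90. Both exceed the half-width.
- With Sp = 0.99 the bias is 6.4 − 6.8 = −0.4 points, well inside it.

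**The case against.** The strongest reply is that this is a condensed article. A scoring rule, a cut-off and a case definition normally sit in the full protocol or analysis plan, and their absence here is no fault. That is correct as far as it goes, and how prevalence will be computed is indeed not stated. But a cut-off only decides who is screen-positive. It does not supply confirmation or impairment data, and Table 1 lists no variable that could.

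The second reply is that the scale is described as serving evaluation as well as screening, is validated in Spanish, has items mapped to the DSM symptoms and is completed by two informants. This stands in part. Suppose each informant had Se 0.80 and Sp 0.90, their errors were independent, and both had to be positive. Then Se = 0.80² = 0.64 and Sp = 1 − 0.10² = 0.99, the screen-positive rate is 0.0435 + 0.0093 = 5.3%, and PPV is 82%. Correlated errors would shrink that gain. So the bias may be small or downward, but the result is still a symptom-based classification.

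A reader might infer two stronger points that the article does not support:

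- **That the sample leaves out children with serious mental disorders in general.** The Exclusion criteria do name "serious physical or mental disorders identified by parents or teachers", but the clause goes on to limit this to disorders that would prevent taking part in the programme, and the Background expressly includes children with ADHD. If 20% of true cases were excluded, an assumption, 6.8% would fall to 0.0544 / 0.9864 = 5.5%. This is a separate, downward and probably small selection effect.
- **That the ADHD subgroup would consist mostly of children without ADHD.** This follows only at lower specificity, below about 0.94 when Se is 0.80. Nothing in the article settles on which side of that value the scale falls.

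**Conclusion.** The mismatch between objective and measurement holds on the article's own text and does not depend on the assumed accuracy figures. What is measured supports the prevalence of a positive rating-scale screen, and a subgroup defined by that screen.

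The size does depend on assumptions. At a true prevalence of 6.8%, the screen-positive rate could be about 5% to 20% over Se 0.60 to 0.90 and Sp 0.85 to 0.99. Neither the direction nor the amount of bias can be fixed from the article, so it would be wrong to say that prevalence will be overstated. The subgroup may contain many children without ADHD, and no more than that can be said.

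The consequence is confined to a secondary descriptive objective and to the label and interpretation of one subgroup. The randomization, the sample size (set on body fat) and the primary comparison are untouched.

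**What to change.** - **Objective (Background).** Restate it as the prevalence of a positive parent-and-teacher screen (ADHD risk) among eligible, consenting children in the two school grades.
- **Subgroup (Statistical analysis, and conclusions drawn from it).** Define it as baseline screen-positive versus baseline screen-negative. Baseline needs to be stated because ADHD risk is also an outcome, measured again at the end of both years, and a later classification could itself be affected by the intervention.
- **Optional.** If a figure for the disorder is still wanted, add a misclassification-corrected range, (screen-positive rate + Sp − 1) / (Se + Sp − 1), with sensitivity and specificity declared as assumptions and varied. As a check, (0.1476 + 0.90 − 1) / (0.80 + 0.90 − 1) = 0.068.

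The two wording changes need no new data. Their cost is a less direct claim: the trial would speak of children at risk on a screen and not of children with ADHD. The optional range would also give a less precise answer than a single rate.

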## Methods/Design

### Study design and participants

A crossover randomized cluster trial was carried out, involving 21 schools located in as many municipalities in the provinces of Cuenca and Ciudad Real, in the Castilla-La Mancha region of Spain. All of them were state-funded schools except for two, which were private. In municipalities with more than one school, only one was selected for the study, to avoid contamination of the intervention. At first, 22 schools were invited, and only one of them refused to participate in the study, arguing that the study could mean excessive administrative overheads for the teachers. After the approval of school councils, the schools were randomly allocated using the statistical package StatsDirect to either the intervention or the control group; finally, the whole sample of schools was divided into three subgroups of randomization as follows: (i) nine public schools from Cuenca, (ii) ten public schools from Ciudad Real, and (iii) two private schools, one in the capital of each province (Fig. 1). All children belonging to the third grade of preschool and first grade of primary school (aged 4 to 7 years) were invited to participate.

**Fig. 1 Fig1:**
[figure not shown]
Flow chart of trial participants. CG, control group; IG, intervention group

#### Inclusion criteria

All participating schools had to have at least two full classrooms for both the third year of preschool and the first grade of primary school. To participate in the intervention and in the measurements at the beginning and end of each academic year, the approval of boards of governors was necessary. All children’s parents or legal representatives signed an informed consent to participate, and were invited to collaborate by filling in questionnaires with regard to family leisure habits, sleeping, eating and getting around town. They completed the questionnaire at home and returned it to the teachers one week later.

#### Exclusion criteria

Children who had any of the following conditions were excluded: (a) severe Spanish language learning difficulties, (b) serious physical or mental disorders identified by parents or teachers that would impede participation in the programme’s activities, or (c) those with diagnoses of chronic disorders, such as heart disease, diabetes or asthma, which in the opinion of their paediatricians would prevent their participation in the programme’s activities.

Schools with only one full third-grade class of preschool or one first-grade class of primary school were excluded.

#### Ethical and legal aspects

The project had the explicit support of the Department of Education and Science of the Junta de Comunidades of Castilla-La Mancha, Spain, who sent a letter to each school that included information about the study. Next, investigators visited each school to explain the aims and methods of the study and to obtain the consent of the head teacher and the school board. This was followed by classroom-by-classroom meetings, in which pupils were asked to collaborate. The Movi-Kids study was also presented to teachers of physical education. Through the teachers, a letter was sent to parents inviting them to a group meeting at the school. In this meeting, the objectives, measurements and procedures of the study were explained, and responses provided to any questions and objections that were raised. Moreover, in this session, informed consent was obtained from all parents for the participation of their children in the study. This document was provided to teachers at the beginning of each academic year.

After each evaluation process, letters with the results of adiposity measures of their children were sent to parents. In those children in which any unhealthy value was detected (e.g., overweight or obesity), the medical research team personally telephoned with parents to give them appropriate recommendations. It was not possible to inform parents immediately about other study variables (e.g., academic achievement or risk of ADHD) because these questionnaires require a more complex analysis.

The study protocol was approved by the clinical research ethics committee of the Virgen de la Luz Hospital in Cuenca and General Universitario Hospital in Ciudad Real. An insurance policy was also signed to cover any potential risks associated with the intervention.

